
#### Software Coordination

The E-Prime software will be integral for stimulus presentation and task control. It will manage the timing of stimulus presentation and coordinate trigger signals to synchronize the eye-tracking and electroencephalography systems. E-Prime will insert data markers into both the eye-tracking and ERP data streams at the beginning and end of each stimulus presentation, ensuring precise alignment of the data during analysis. For temporal accuracy, eye-tracking data will be aligned with ERP data using timestamps from the synchronization triggers, ensuring that each data point from the eye-tracker corresponds to the same point in time as the neural data. Any potential latency differences between the systems will be identified and corrected during the data analysis phase using these synchronized timestamps. A custom script in MATLAB will integrate the eye-tracking and ERP data based on synchronization markers provided by E-Prime.

### Questionnaires

#### Demographic

The demographic questionnaire will be used to collect baseline information on participants to ensure that the study population is adequately characterized. The demographic questionnaire will collect information on age, gender, education level, socioeconomic status, smoking status, etc. The data gathered will be used for descriptive statistics, to stratify analyses, and to ensure that participants meet eligibility criteria.

#### Food Choice Questionnaire

Participants will be asked to self-report their final selection from the food items presented during the study. They will also be asked to complete a 36-item FCQ [32] for each familiar or novel item in each food group. FCQ consists of 9 subscales designed to assess the significance of various factors influencing food choices. These subscales measure the importance of health considerations, convenience in terms of preparation and purchase, price and value for money, sensory appeal (including taste, smell, and texture), natural content and the absence of additives, mood regulation, and the use of food to manage stress, familiarity with the food, ethical concerns related to origin and packaging, and weight control (the questionnaire can be found in Multimedia Appendix 2).

#### Data Management

All data collected during the study will be securely stored and managed to ensure participant confidentiality and data integrity. Each participant’s data will be assigned a unique identifier to maintain anonymity. Data from the dot-probe task, eye-tracking, and electroencephalography recordings will be directly entered into secure, password-protected databases. Data entry will be verified by cross-checking with the original source files to ensure accuracy. All electronic data will be stored on encrypted servers with regular backups. Physical data, such as consent forms, will be stored in locked cabinets accessible only to authorized personnel. Access to the data will be restricted to the research team members directly involved in the study. Any data sharing with external collaborators will be conducted under strict data-sharing agreements ensuring confidentiality and compliance with ethical standards.

### Statistical Analysis

ERP data will be preprocessed with EEGLAB v14.1.2 toolbox for MATLAB [33], involving noise removal, epoching from stimulus onset to 1000 milliseconds post stimulus, and averaging across epochs to extract ERP components. Potentials reflecting ocular or muscle-related artifacts were removed using logistic infomax independent component analysis [34]. Further artifacts will be removed using the clean_rawdata plugin for EEGLAB.

Regarding dot-probe and electroencephalography attention-related measures (RTs, and N100 and P300 amplitudes, respectively), repeated measures ANOVA will be conducted, including the stimulus type (familiar vs novel across 4 food categories) as a within-subject factor, and group (500 ms vs 2000 ms) as a between-subject factor. Similarly, ANOVA will also be conducted to examine eye-tracking measures (TTFF, FD) between groups (500 ms vs 2000 ms). Post-hoc analyses will be conducted with Bonferroni adjustments for multiple comparisons. In addition, relationships between eye-tracking measures (TTFF, FD) and ERP components (P300 and N100 amplitudes) will be calculated by the Spearman correlation analysis. IBM SPSS Statistics 20 (IBM Corp) software will be used to analyze the data. No interim analyses are scheduled for this study.

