### Sample Size

An a priori power analysis was conducted using G Power version 3.1.9.7 (Department of Psychology, Heinrich Heine University Düsseldorf) to determine the appropriate sample size needed to achieve sufficient statistical power for our study. The analysis was designed for an *F* test, with an assumed medium effect size of *F*=0.35, a significance level of α=.05, and a desired statistical power of 0.80. Based on these parameters, the calculated sample size required was 40 participants. Specifically, the number of groups (between-subject factor) was set at 2 (500 ms vs 2000 ms), and the number of measurements (within-subject factor) included 8 (2 stimulus types [familiar or novel] across 4 food categories). In addition, the correlation among repeated measures was conservatively set at 0.5. The medium effect size was chosen based on the existing literature on attentional bias studies, which commonly report medium to large effect sizes [23]. Under these specifications, G Power estimated an achieved power of 0.820, exceeding the commonly accepted threshold of 0.80 for adequate power. This indicates that a sample size of 40 participants is sufficient to detect a medium effect size in our primary outcome using repeated measures ANOVA, ensuring the study is powered to identify meaningful changes while balancing feasibility within the constraints of a pilot study.

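### For RT, N100 and P300 the plan folds food category into a single within-subject factor, so its overall test, read literally, does not isolate familiar versus novel

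*Protocol article*

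**What the plan says.** The Statistical Analysis section of the protocol article describes the ANOVA for reaction time (RT), N100 and P300 as "including the stimulus type (familiar vs novel across 4 food categories) as a within-subject factor", with presentation time (500 or 2000 ms) between subjects. The Sample Size section matches this. It enters presentation time as two groups, and its within-subject entry reads "the number of measurements (within-subject factor) included 8 (2 stimulus types [familiar or novel] across 4 food categories". Both passages speak of one within-subject factor, and the count attached to it is 8.

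Neither section lists food category as a factor, or names a familiarity main effect or a familiarity-by-presentation-time term as the test that answers the question. Follow-up is given in one sentence: "Post-hoc analyses will be conducted with Bonferroni adjustments for multiple comparisons". The set of comparisons to be corrected is not stated.

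The questions themselves concern familiarity. The Introduction and Principal Findings predict differences between familiar and novel foods in RT and P300. The Primary Outcome is the familiar-novel difference at different presentation times. No hypothesis concerns differences between milk, oil, sauce and beverages.

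**The concern.** A single factor made of the 2 x 4 combinations of familiarity and category has eight levels and 7 degrees of freedom. One is familiar versus novel, three are differences among categories, and three are the category-by-familiarity interaction. A significant result for such a factor shows only that some of the eight cells differ.

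Category differences are plausible here. Visual Stimuli Selection matches pictures for shape, color, position and background within each pair, and promises no such matching across categories. The Outcome Measures textbox describes N100 as linked to early sensory processing, so it could respond to how the pictures look.

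Three things are at stake. A significant factor could be reported as a familiarity finding when it is a category finding. A small, uniform familiarity effect is diluted over 7 degrees of freedom. And if the follow-up covers every pair of cells, most of the Bonferroni correction is spent on comparisons such as familiar milk versus novel oil, which answer no question in the protocol.

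**Working it through.** **Inputs from the Sample Size section:** "the calculated sample size required was 40 participants"; two groups; m=8 measurements; effect size f=0.35; "a significance level of α=.05, and a desired statistical power of 0.80"; "the correlation among repeated measures was conservatively set at 0.5".

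**Assumptions of this check:** 20 participants per group, cell SD of 1, equal correlations (so sphericity holds), and the effect sizes below. The protocol gives no SDs and no category differences. Power comes from the noncentral F distribution.

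**1. The plan's own figure.** The stated power of 0.820 reproduces as the between-subject effect:
- noncentrality = f² x N x m / (1 + (m−1) x rho) = 0.1225 x 40 x 8 / 4.5 = 8.711
- df 1 and 38, power 0.8202
- N=38 gives 0.799, so 40 is the smallest even N that reaches 0.80.

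The eight-measurement within-subject test at the same f has noncentrality 0.1225 x 40 x 8 / 0.5 = 78.4 on df 7 and 266, with power above 0.999. The printed 0.820 therefore belongs to 500 versus 2000 ms and not to a familiarity test.

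**2. Degrees of freedom.** Eight levels give 8−1 = 7 = 1 (familiarity) + 3 (category) + 3 (interaction). The error df are 38 x 7 = 266. The familiarity contrast alone has df 1 and 38.

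**3. No familiarity effect, one category shifted by s.** The variance of the cell means is s² x (1/4) x (3/4), so the noncentrality is 0.1875 s² x 40 x 8 / 0.5 = 120 s².

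| s (SD) | f | Noncentrality | 7-df test rejects |
|---|---|---|---|
| 0.2 | 0.087 | 4.8 | 29% |
| 0.3 | 0.130 | 10.8 | 64% |
| 0.4 | 0.173 | 19.2 | 91% |

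In 4,000 simulated trials per scenario, the 7-df test rejected in 30%, 64% and 91%, while the 1-df familiarity test stayed near 5%.

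**4. Uniform familiarity difference d, no category effect.** Here f = d/2, so the noncentrality is (d/2)² x 40 x 8 / 0.5 = 160 d².

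| d (SD) | Noncentrality | 1-df familiarity test | 7-df test |
|---|---|---|---|
| 0.20 | 6.4 | 69% | 39% |
| 0.227 | 8.27 | 80% | 50% |
| 0.25 | 10.0 | 87% | 60% |
| 0.30 | 14.4 | 96% | 79% |
| 0.70 (f=0.35) | 78.4 | >99.9% | >99.9% |

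**5. Follow-up.** Eight cells give 8 x 7 / 2 = 28 pairs. Four are familiar-novel pairs within a category; the other 24 are not. For one within-category difference of dz=0.5 (paired t test, n=40), power is 44% at 0.05/28 and 70% at 0.05/4. The 28-pair family is an assumption, since the protocol names none.

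**The case against.** The strongest reply is that an eight-level factor is never stated. The Sample Size section counts two stimulus types, the Abstract says the ANOVA examines familiarity and novelty, and a proper 2 x 4 design also has 8 measurements. The phrase could be shorthand for that factorial, or for averaging over category, and either would give a 1-df familiarity test. This stands: the literal reading is the most direct one, but not the only one. A journal article may also leave coding detail to an analysis plan. Still, the article does state a factor structure, in two places that agree, and the structure it states leaves category out.

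A reader might infer that the planned analysis will miss real familiarity effects. The documents do not support that. The loss applies to effects well below the planned size: the 7-df test has 79% power at 0.30 SD and over 99.9% at f=0.35, if all of that effect is familiarity.

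A reader might also infer that the authors will report any significant overall test as a familiarity effect. Nothing says so, and post-hoc comparisons are planned that could show which cells differ. Against that, their family is open, and no single pair of cells tests the overall familiarity effect.

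Finally, the point does not reach the eye-tracking measures. Their ANOVA is described separately, as a comparison between the presentation-time groups.

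**Conclusion.** The point holds as a should-fix matter for RT, N100 and P300, and does not prove that a wrong analysis will be run. As written, the within-subject factor combines familiarity with category, and its overall test is not specific to the protocol's hypotheses. The serious consequence is misattribution: rejection in 29% to 91% of trials for an assumed single-category shift of 0.2 to 0.4 SD with no familiarity effect. High power at f=0.35 does not cure that, because the problem is what a significant result means. The power loss is secondary and confined to small effects (80% to 50% at about 0.23 SD). The follow-up loss (70% to 44% at dz=0.5) applies only if all 28 pairs are corrected. All of these figures rest on N=40, correlation 0.5 and sphericity. If a 2 x 4 factorial with a 1-df familiarity test was intended, the remaining defect is that the text does not say so.

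**What to change.** In both the Sample Size and Statistical Analysis sections:
- State familiarity (2 levels) and food category (4 levels) as separate within-subject factors, with presentation time alongside them.
- Base conclusions about familiarity on the 1-df familiarity effect and its interaction with presentation time, and treat the category main effect as a nuisance term. With two levels, the familiarity contrast needs no sphericity correction.
- Limit the Bonferroni follow-up to the four within-category familiar-novel contrasts.
- Say which effect the power of 0.820 refers to, since it reproduces only for 500 versus 2000 ms.

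The cost is a sentence or so in each section and a different factor definition in SPSS. No new data are needed, and the Abstract reports that analysis had not begun at submission.

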**Methods:**

A total of 40 healthy adult participants will be recruited. Participants will be presented with pairs of familiar or novel food images, while their visual attention and brain activity are recorded concurrently. Eye-tracking metrics, including time to first fixation and total fixation duration, will be used to assess visual attention. Electroencephalography data will be collected to measure the amplitude of event-related potential components, such as P300 and N100, associated with attentional processing. Reaction times will also be recorded as a behavioral measure of attentional engagement with familiar versus novel food items. Data analysis will involve repeated measures ANOVA to examine the effects of food familiarity and novelty on attentional bias metrics. Correlation analyses will also be conducted to explore the relationships between eye-tracking, electroencephalography, and dot-probe measures.

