While some previous studies have suggested a role for visual attentional bias toward familiarity and novelty of stimuli [22], there is a paucity of studies using electroencephalography to examine this, particularly in the context of food choice behavior. Electroencephalography is a noninvasive technique used to measure brain activity in response to stimuli by recording event-related potentials (ERPs). So far, only a few studies have explored integrating electroencephalography, eye-tracking, and dot-probe methods to study attentional bias to food-related stimuli [23]. Of note, no previous study has taken stimulus novelty and familiarity into consideration, nor how the results of this integrated approach associate with the self-report food choices. Familiar stimuli evoke trust and perceived quality from previous positive experiences are suggested to influence an individual’s choices [24]. However, novel products require more cognitive effort to evaluate, leading to longer information processing times [25]. Thus, the main objective of this pilot study is to examine differences in attention to novel compared with familiar food stimuli, using 3 different attention indexes, including electroencephalography, eye tracking, and dot-probe. Indeed, it is hypothesized that participants will exhibit shorter reaction times (RTs) and longer total fixation durations (TFDs) for familiar compared to novel food items, indicating a stronger attentional bias toward familiar foods. In addition, familiar food items will elicit greater P300 amplitudes compared with novel food items, suggesting enhanced attentional engagement and processing.

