### Outcomes

#### Primary Outcome

The primary outcome includes identifying the difference in 3 attentional bias metrics toward familiar or novel food stimuli at different presentation times. Detailed descriptions of these outcome measures are provided in the “Outcome Measures” section below.

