**Total fixation duration (TFD)**
The cumulative time spent fixating on a target during a given trial. TFD reflects the allocation and engagement of attention over time. A longer TFD on a target implies greater sustained attention and interest, indicating how engaging or relevant the stimulus is perceived to be. This measure elucidates how familiarity affects sustained visual attention toward different products [27].

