#### Eye Tracking

The eye-tracking component of this study will be conducted using the Tobii Nano Pro (Tobii Tech), a screen-based eye tracker known for its high precision in capturing gaze data. The Tobii Nano Pro offers a sampling rate of 60 hertz, which translates to data collection at intervals of 16.67 milliseconds. This high frequency allows for detailed tracking of eye movements and gaze patterns. To ensure accurate gaze data, a standard 9-point calibration procedure will be performed at the beginning of each session. This process involves directing the participant’s gaze to 9 specific points on the screen to map their eye movements accurately. The calibration will be verified for precision before starting the main trials to ensure reliable spatial and temporal tracking. Participants will be seated approximately 60 cm from the Tobii monitor, which has a resolution of 1600 × 1200 pixels. Participants will be instructed to maintain a still head position and focus attentively on the images displayed on the screen. Participants will view pairs of pictures displayed side by side for 500 or 2000 milliseconds each. Each image pair is matched for shape, color, and background to control for these variables. The following eye-tracking parameters will be measured:

TTFF: time elapsed between the appearance of a picture and the user’s initial gaze fixation within an area of interest. In this case, each product will be defined as a separate area of interest.First fixation duration: time participants gaze at their first fixation point.TFD: length of all fixations within a specific area of interest (in seconds). Average TFD will be used for statistical analyses.Fixation count: number of fixations on stimuli.Eye movement data will be analyzed using Tobi software.

Fixations are defined as periods where the gaze remains stable within a 30-pixel radius for at least 100 milliseconds, and these fixations must be initiated at least 100 milliseconds after picture onset to exclude anticipatory eye movements.

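### The eye-tracking ANOVA names only the 500 ms versus 2000 ms comparison, which display length largely determines for total fixation duration, and leaves the familiar-versus-novel factor unnamed

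*Protocol article*

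**What the plan says.** The Introduction of the protocol article predicts that "participants will exhibit shorter reaction times (RTs) and longer total fixation durations (TFDs) for familiar compared to novel food items"; the Discussion repeats this. The Primary Outcome section defines the target as "identifying the difference in 3 attentional bias metrics toward familiar or novel food stimuli at different presentation times".

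For reaction times, N100 and P300, the Statistical Analysis section sets out a repeated measures ANOVA in these terms: "including the stimulus type (familiar vs novel across 4 food categories) as a within-subject factor, and group (500 ms vs 2000 ms) as a between-subject". The next sentence turns to eye tracking. It opens with the word *Similarly*, but the only comparison it states is "ANOVA will also be conducted to examine eye-tracking measures (TTFF, FD) between groups (500 ms vs 2000 ms".

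The Outcome Measures textbox defines TFD as "The cumulative time spent fixating on a target during a given trial". The Eye Tracking section gives it in seconds, says its average is what will be analysed, and states no scaling to display time. It requires a fixation to last at least 100 ms, and says "these fixations must be initiated at least 100 milliseconds after picture onset". It lists first fixation duration and TFD as separate measures. The abbreviation list expands FD only as fixation duration, so the analysis sentence does not show which of the two is meant.

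**The concern.** There are two separate problems.

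First, the eye-tracking sentence, read on its own, compares people shown pictures for 500 ms with people shown them for 2000 ms. That contrast says nothing about whether gaze favours the familiar picture.

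Second, if FD is TFD, the design largely settles the result. A person who can look for 2000 ms accumulates more fixation seconds than one who can look for 500 ms, whatever attracts attention. The group effect would then be significant almost regardless of the data, and it could be reported as a finding about sustained attention in one of the three primary metrics.

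Naming the familiarity factor solves the first problem and only part of the second. The primary outcome asks about bias at different presentation times. In raw seconds, the same proportional preference gives a larger familiar-minus-novel difference on the longer display.

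**Working it through.** **1. The plan's own figure.** The Sample Size section gives f = 0.35, α = 0.05, two groups (500 ms and 2000 ms), m = 8 measurements, correlation ρ = 0.5, N = 40 and power 0.820. As a between-group main effect:

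λ = f²·N·m / (1 + (m − 1)ρ) = 0.1225 × 40 × 8 / 4.5 = 8.71, with 1 and 38 df, giving power 0.8202. N = 38 gives 0.799.

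The stated figure is reproduced. As a within-subject effect, λ = f²·N·m / (1 − ρ) = 39.2 / 0.5 = 78.4, and power exceeds 0.999, which does not match. The study was therefore sized on the same duration contrast that the eye-tracking sentence names.

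**2. Ceilings on countable fixation time.** Inputs are the display times and the 100 ms earliest start, both from the Eye Tracking section. Fixations are assumed to count only while the pictures are shown. Summed over the two pictures:

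- 500 ms display: 500 − 100 = 400 ms
- 2000 ms display: 2000 − 100 = 1900 ms
- ratio: 1900 / 400 = 4.75

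**3. Interaction in raw seconds.** Assume, for illustration, that 55% of fixation time goes to the familiar picture at both durations and that all countable time is spent on the two pictures. Neither assumption comes from the documents, and the second makes the results upper bounds.

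- 500 ms: (0.55 − 0.45) × 400 = 40 ms
- 2000 ms: (0.55 − 0.45) × 1900 = 190 ms
- apparent interaction: 190 − 40 = 150 ms, with no change in preference

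**4. Illustrative simulation.** 20 people per group, 3000 runs per setting, attention identical in both groups. Assumed share of fixation time on the familiar picture: mean 0.55, SD 0.08. The assumed share of countable time spent fixating varies by row. Entries are the percentage of runs significant at 0.05.

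| Share of time fixating, mean (SD) | Group effect, raw | Group effect, proportion | Interaction, raw | Interaction, proportion |
|---|---|---|---|---|
| 0.6 (0.15) | 100 | 4.5 | 53.3 | 4.7 |
| 0.7 (0.20) | 100 | 5.4 | 51.9 | 5.3 |
| 0.5 (0.25) | 100 | 5.9 | 45.9 | 4.4 |

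Proportion here means TFD divided by countable viewing time. On that scale both tests hold close to 5%.

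**5. TTFF.** An early first fixation has the same TTFF on either display, so longer display does not inflate it. On the 500 ms display, a picture not reached before offset has no value. The latest recordable TTFF is 500 ms, or 500 − 100 = 400 ms if the minimum fixation must finish before the pictures disappear, a rule the article does not state. The 2000 ms display keeps later first fixations, so the two groups' averages cover different ranges.

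**The case against.** The strongest reply is that familiarity is intended for eye tracking. *Similarly* follows directly on a sentence that names stimulus type as a within-subject factor. The abstract plans "repeated measures ANOVA to examine the effects of food familiarity and novelty on attentional bias metrics" without excepting eye tracking. The Intervention section says gaze data will quantify attention to familiar versus novel items, and the Sample Size section describes eight cells that include stimulus type. This stands. A reader might infer that the fixation hypothesis will not be tested at all; the documents do not support that, because the factor is unnamed, not excluded. Nor does reproducing the sample size on the duration contrast prove that familiarity was left out.

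A reader might also infer that raw seconds spoil every eye-tracking test. They do not. Both pictures share each trial and have the same exposure, so the familiarity main effect, which is the hypothesised contrast, remains interpretable. Only the group effect and the interaction depend on scale. The interaction argument assumes a constant proportional preference, and in the simulation false significance arose in about half the runs, not all.

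A third tempting reading is that TTFF differs by construction just as TFD does. It does not; it is truncated, which is a smaller problem. The 4.75-fold ceiling is also specific to TFD. First fixation duration is capped by the display too, but less severely.

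Finally, a condensed article may leave the scaling of a derived variable to an analysis plan. That has some force, but this article does state the unit, the summary to be analysed and the comparison, and those stated choices are what conflict with the hypothesis.

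**Conclusion.** The point holds in this form. The eye-tracking analysis as written names only the duration contrast and not the familiar-versus-novel factor that the hypothesis and primary outcome require. If FD is TFD in average seconds, that contrast is determined largely by display length (ceilings of 400 ms and 1900 ms, 4.75-fold) and cannot be read as attention. A raw group-by-familiarity interaction would be driven by scale in the same way, at most 40 ms against 190 ms under the assumed 55:45 split.

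The ceilings follow from the article's own rules, provided that counting stops at picture offset. The 55:45 split and the simulation inputs are assumptions. The conclusion does not extend to the familiarity main effect, and it applies to TTFF only to a lesser degree. The wording should be corrected before analysis begins, because a primary metric would otherwise yield a near-certain but uninformative group difference.

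**What to change.** In the Statistical Analysis section:

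1. Name stimulus type (familiar versus novel) as a within-subject factor for the eye-tracking measures, as is done for reaction times and ERP amplitudes.
2. State whether FD is first fixation duration or TFD.
3. Compare TFD across durations only as familiar / (familiar + novel) or as a proportion of available viewing time, or else analyse it within each duration. State that the raw TFD group effect will not be interpreted as attention.
4. Compare TTFF across durations only within a common window, the first 500 ms after picture onset.

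The cost is analysis wording. All quantities come from gaze data already being recorded, and the abstract says analysis has not started, so the rule can still be fixed without knowledge of the results.

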## Methods

### Objectives

The secondary objectives of this study are to obtain preliminary data on the quality of the data, along with the potential correlations between visual attention metrics as assessed by eye tracking, RTs in response to the dot-probe task, and amplitude of ERP components. In addition, an exploratory objective of this study is to investigate the association between the data of attentional bias tools with the self-reported food choice to further our understanding of the potential of ERP and eye-tracking data in predicting the individual’s ultimate food choice, particularly taking stimulus familiarity into consideration.

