#### Secondary Outcomes

The secondary outcomes focus on evaluating the correlations between ERP data obtained from electroencephalography recordings and the metrics captured through eye tracking and RTs from the dot-probe task.

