### Data Collection Plan

#### Dot-Probe Task

The dot-probe task will be implemented using E-Prime 3.0 software (Psychology Software Tools, Inc) for both eye-tracking and ERP components. Each trial will commence with a 500-millisecond presentation of a fixation cross at the center of the screen. This serves to focus participants’ attention on the central point before the food stimuli are displayed. Following the fixation cross, a pair of images (one familiar and one novel) will be shown side-by-side for either 500 or 2000 milliseconds. The side on which each type of image appears is randomized to control for location bias. After the image pair is presented, a dot-probe will appear in the location previously occupied by one of the images. The dot will remain visible for 500 milliseconds. Participants will indicate the location of the dot by pressing the “L” key if the dot appears on the left side of the screen, or the “R” key if it appears on the right side. The response time and accuracy will be recorded for each trial (Figure 1).

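### The Spearman analysis omits the RT–ERP correlations named in the secondary outcome and does not say how the two presentation times are kept apart

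*Protocol article*

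**What the plan says.** All references are to the protocol article.

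- **Secondary Outcomes** aims at "correlations between ERP data obtained from electroencephalography recordings and the metrics captured through eye tracking and RTs from the dot-probe task". ERP is to be related to two things: eye tracking and RT.
- **Objectives** lists "potential correlations between visual attention metrics as assessed by eye tracking, RTs in response to the dot-probe task, and amplitude of ERP components", that is, all three modalities.
- **Abstract, Methods** says: "Correlation analyses will also be conducted to explore the relationships between eye-tracking, electroencephalography, and dot-probe measures".
- **Statistical Analysis**, the only place that specifies the correlation analysis, says that "relationships between eye-tracking measures (TTFF, FD) and ERP components (P300 and N100 amplitudes) will be calculated by the Spearman correlation analysis". RT is not in that list.
- The same section enters "group (500 ms vs 2000 ms) as a between-subject factor" in the ANOVAs. The correlation sentence mentions neither a split by presentation time nor an adjustment for it.
- **Dot-Probe Task** says that image pairs "will be shown side-by-side for either 500 or 2000 milliseconds", without saying who sees which.
- **Outcome Measures** defines total fixation duration as "The cumulative time spent fixating on a target during a given trial".

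**The concern.** There are two separate problems.

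**Coverage.** The analysis sentence names its variables as a closed list, and the list is shorter than the outcome it serves. An analyst who follows it would relate eye tracking to ERP and stop there. The RT–ERP part of a named secondary outcome would have no planned analysis.

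**Presentation time.** Fixation time is limited by how long the pictures are shown. If ERP amplitude also differs between the two presentation times, a single rank correlation over all participants picks up the difference between groups. It can then be significant even if, within each group, people who fixate longer have no larger or smaller ERP. Principal Findings already anticipates that eye-tracking measures will correlate with ERP components, so such an artefact could be read as confirmation.

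**Working it through.** **1. Count of pairs.**
- Statistical Analysis: 2 eye-tracking measures × 2 ERP components = 4.
- Secondary Outcomes adds RT–P300 and RT–N100: 4 + 2 = 6.
- Abstract and Objectives also suggest RT–TTFF and RT–FD: 6 + 2 = 8.

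**2. The plan's own figure.** No power is given for the correlations. The only computed design figure is the 0.820 in Sample Size, from N = 40, f = 0.35, 8 measurements, correlation 0.5, 2 groups and α = 0.05. With the between-group formula for repeated measures:

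λ = N·f²·m / (1 + (m − 1)ρ) = 40 × 0.1225 × 8 / 4.5 = 8.71, with 1 and 38 degrees of freedom, gives power 0.8202.

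This reproduces 0.820. The within-subject and interaction formulas give about 1.00, so the protocol's effect size is that of the 500 v 2000 ms comparison. For two equal groups d = 2f = 0.70. I use this as the reference ERP difference; the article does not state one for ERP itself.

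**3. Can fixation time differ by group?** Eye Tracking counts only fixations that begin at least 100 ms after picture onset. If only the picture display counts, fixation time is at most 500 − 100 = 400 ms in one group and 2000 − 100 = 1900 ms in the other. A large separation is plausible for fixation duration. TTFF is not limited in the same way, so smaller shifts are relevant there.

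**4. False-positive rate of one correlation over all participants.** Assumptions, none given in the article: 20 participants per presentation time, normal data, and zero correlation between eye tracking and ERP within each group. Group differences are in SD units. The test is two-sided at 5%, with 10,000 simulated data sets per cell.

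| Eye-tracking shift | ERP 0 | ERP 0.3 | ERP 0.5 | ERP 0.7 | ERP 1.0 |
|---|---|---|---|---|---|
| 0 SD | 4.7% | 5.0% | 5.0% | 5.4% | 4.7% |
| 1 SD | 5.0% | 6.9% | 9.7% | 14.9% | 24.5% |
| 2 SD | 4.9% | 10.2% | 19.5% | 32.6% | 56.4% |
| 4 SD | 4.9% | 12.2% | 25.6% | 43.3% | 72.2% |

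At an ERP difference of 0.7 SD the mean spurious coefficient is 0.15, 0.24 and 0.28 for eye-tracking shifts of 1, 2 and 4 SD.

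Simulation error (95%) is 1.96 × √(0.149 × 0.851 / 10,000) = 0.7 points at 14.9%, and 1.96 × √(0.433 × 0.567 / 10,000) = 1.0 point at 43.3%. Hence about 14% to 44% at d = 0.70.

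**5. The same data with presentation time taken into account.** Ranking within each group and testing the combined coefficient on 37 degrees of freedom gives rejection of 4.5% to 5.3% in every setting.

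**The case against.** The strongest reply concerns the second problem. A reader might infer that the plan pools raw values over both presentation times. The article does not say so: it is silent, and a fuller analysis plan could settle the matter. That stands, so the point here is a missing safeguard and not a stated error.

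Nor is it established that the correlations would be significant because of duration. Both measures must differ, and where ERP does not, the rate stays near 5%. The article gives mixed signals on ERP. Statistical Analysis takes epochs from stimulus onset. If that means picture onset, the two displays are identical for the first 500 ms, which covers N100 (about 100 ms) and most of the P300 window (300–600 ms). Electroencephalography Acquisition instead starts epochs at the dot, which follows a preview four times as long in one group (2000 / 500); a difference is then possible for both components. The risk therefore varies over the four planned pairs. It is clearest for fixation duration with P300, and weaker for TTFF.

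The 20 + 20 split is also an assumption. If each participant saw both presentation times and values were averaged per person, rejection would be about 5% (5.2% to 5.6%). If each person contributed two rows, it would be 46% to 98% for ERP shifts of 0.5 to 1.0 SD and an eye-tracking shift of 4 SD.

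A reader might further infer that only familiar-minus-novel scores are valid here. The documents do not support that. Objectives and Secondary Outcomes ask for correlations of the measures themselves. The two pictures appear together, so a picture-locked ERP has no separate familiar and novel amplitude to subtract.

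On the omission of RT, the only reply is that the Abstract promises dot-probe correlations, so they may still be run. That shows intent, but it leaves the article inconsistent with itself.

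**Conclusion.** The omission of RT is certain: the analysis section covers 4 pairs, while Secondary Outcomes needs 6 and the Abstract and Objectives point to 8.

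The presentation-time problem is real but conditional. It needs one correlation over all participants, and a difference by presentation time in both the eye-tracking measure and the ERP. With 20 per group and the protocol's own design effect applied to ERP (d = 0.70), the false-positive rate is about 14% to 44% against a nominal 5%, for eye-tracking shifts of 1 to 4 SD. With no ERP difference there is no inflation. The correlations are exploratory in a pilot study, which limits the consequences. One sentence would remove the risk, and the article reports that analysis has not begun.

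**What to change.** Replace the correlation sentence in Statistical Analysis with one that does two things:

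1. **Lists all the pairs.** Keep TTFF and FD with P300 and N100. Add RT–P300 and RT–N100 to meet Secondary Outcomes, and RT–TTFF and RT–FD to match the Abstract and Objectives.
2. **Handles presentation time.** State that every correlation is computed within each presentation time, or as a partial rank correlation adjusted for it, with one value per participant and measure in each analysis.

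Familiar-minus-novel scores can be added as an optional sensitivity analysis where they can be formed: RT by probe location, share of fixation time, and probe-locked ERP. They are noisier than the measures themselves, so coefficients may be smaller.

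The cost is small and no new data are needed. There are four more pairs to report. Adjustment loses one degree of freedom (37 instead of 38 with 40 participants); analysis within each presentation time leaves about 20 per stratum if the groups are equal, with correspondingly less precise coefficients.
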